### Data management {26}

Data collected as part of this trial includes questionnaires, surveys, qualitative data from interviews and video data (audio and visual). REDCap and Qualtrics will be used for electronic data capture. Validation will be built into these systems to ensure accuracy, completeness and reliability. Interviews and focus groups will be transcribed verbatim by a service compliant with UK GDPR. Data integrity is maintained through regular validation reports with all discrepancies fully documented and resolved.

The Universities of York, Kent and Sheffield will be involved in the handling of data. All data will be restricted to those individuals who require access in order to fulfil the responsibilities of their role in the trial.

All data will be kept strictly confidential with access restricted to necessary team members only. Video data (audio and visual) will be stored at the University of Kent or the University of York. All questionnaire data will be collected electronically using a mixture of REDCap and Qualtrics either via self-completion or with assistance from a trial support officer over the phone. All electronic questionnaire data will be stored on a secure password-protected server located at the University of York. Any data captured on paper, e.g. session record logs, will be entered onto the electronic system, after which paper copies will be stored in a locked filing cabinet in a room with restricted access at the University of York. Paper copies of questionnaires will be destroyed at the end of the trial (expected June 2027). All personal data will be destroyed 10 years after completion of the trial whilst anonymised data will be retained indefinitely.

### Confidentiality {33}

All information collected during the course of the study will be kept strictly confidential. All identifiable participant data will be coded, pseudonymised by participant number in all manual and electronic files and no participant identifiable data will be transferred from the database to the statistician. Output for analysis will be generated in a format, and at intervals, to be agreed between YTU and the chief investigators. Data will be stored on University of York computers with restricted access; these will all be password-protected.

All data will be collected and retained in accordance with the UK General Data Protection Regulation, Data Protection Act 2018 and YTU Standard Operating Procedures (SOPs).

## Statistical methods

### Statistical methods for primary and secondary outcomes {27a}

Statistical analyses will be conducted using Stata v19 or later (to be confirmed in the final report) and will be reported in line with the Consolidated Standards of Reporting Trials (CONSORT) 2025 statement, adjusted for a cluster RCT. The analysis will be undertaken according to the principles of intention to treat (ITT). The flow of settings and children/young people through the trial will be presented in a CONSORT diagram. The number of settings approached, recruited and randomised will be presented alongside the number of children/young people and parents/carers identified as eligible for the evaluation, approached and recruited. The number of educational settings and/or participants who withdraw from the intervention and/or trial will be presented, alongside reasons for withdrawal, if available. All baseline data will be summarised descriptively by group. No formal statistical comparisons for baseline imbalance will be undertaken. Continuous data will be presented using a mean and standard deviation and categorical data will be presented using a count and a percentage. All outcomes will be reported descriptively at all follow-up time points.

#### Primary analysis

The primary analysis will compare the optimal CCS score between groups using a covariance pattern mixed linear model, incorporating all post-randomisation time points (32 and 52 weeks). The model will adjust for minimisation factors, baseline optimal CCS score, time, treatment arm, treatment-by-time interaction and other relevant baseline covariates as fixed effects, with educational setting and child/young person as random effects to account for the clustering by setting and repeated observations per participant. The correlation of observations within participants over time will be modelled by a covariance structure. The Akaike information criterion will be used to compare models specifying different covariance structures (smaller values preferred). Model assumptions will be checked, and if they are in doubt, the data will be transformed prior to analysis. The treatment effect overall and at both time points (32- and 52 weeks) will be extracted in the form of an adjusted mean difference, 95% confidence interval and *p* value. The primary timepoint of interest is 32 weeks post-randomisation.

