### Participant timeline {18}

Participants will be enrolled in the study and the baseline assessment completed in the autumn term (September to December). The intervention will be delivered during spring and summer terms (January to May). Data will be collected 32 weeks post-randomisation (June–July) and 52 weeks post-randomisation (November–December).

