### Sample size {19}

The primary outcome is the CCS at 32 weeks. A study utilising the CCS for communication skills of children with autism spectrum disorder who were minimally verbal [13] indicated that a 1-point increase in scores is a minimal clinically important difference (MCID). Assuming a MCID of one point on the CCS [13], a standard deviation of 2.08 [12], 90% power, 5% alpha, 20% loss to follow-up at the child/young person level, 10% drop out at the educational setting level, ICC = 0.09 (calculated from a similar trial published by the trial team, [22] and an average cluster size of 5, we would need to randomise 66 educational settings (330 children and young people). Sample size calculations were conducted in Stata v17 using the command clustersampsi. The Stata code used to determine the number of educational settings is given as follows:clustersampsi, mu1(0) mu2(1) sd1(2.08) sd2(2.08) m(4) rho(0.09) beta(0.9)with further adjustment to the number of educational settings to allow for up to 10% attrition.

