#### Secondary analyses

A similar approach to the primary analysis will be adopted for the secondary outcomes, adjusting for baseline scores where appropriate.

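### The primary model lets the treatment effect vary by visit but assumes one baseline CCS slope for weeks 32 and 52; a baseline-by-time term would remove that assumption at almost no cost

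*Protocol article*

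**What the plan says.** In the protocol article, the Primary analysis section fits a covariance pattern mixed model "incorporating all post-randomisation time points (32 and 52 weeks"), with baseline as a covariate and not as an outcome. Besides the minimisation factors, the fixed effects are "baseline optimal CCS score, time, treatment arm, treatment-by-time interaction and other relevant baseline covariates as fixed effects". On the within-child covariance it says: "The Akaike information criterion will be used to compare models specifying different covariance structures (smaller values preferred"). Treatment effects are to be extracted overall and at each visit, and "The primary timepoint of interest is 32 weeks post-randomisation".

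The Secondary analyses section extends the approach: "A similar approach to the primary analysis will be adopted for the secondary outcomes, adjusting for baseline scores where appropriate". Under Outcomes, the 52-week optimal CCS score is itself a secondary outcome. Participant timeline {18} puts baseline in the autumn term, and then: "Data will be collected 32 weeks post-randomisation (June–July) and 52 weeks post-randomisation (November–December").

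**The concern.** The list names one time interaction (treatment) and gives baseline CCS only a main effect. The open-ended reference to further baseline covariates does not supply a baseline-by-time term. As written, a one-point difference at baseline predicts the same difference at both follow-ups.

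The calendar gives some reason to doubt this. Baseline and week 32 fall in one school year. Week 52 comes 20 weeks later, in the next school year. The CCS is scored from a video of the child with the associated teacher, so a change of teacher between years could weaken the link further, though the article does not say that this happens.

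If the slopes differ, the shared slope is a compromise that is not the best adjustment at either visit. What is at stake is a small amount of precision at each visit, and a small remainder of any chance baseline imbalance in the visit-specific estimates and in their difference.

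**Working it through.** **The plan's own figure.** Sample size {19} gives "clustersampsi, mu1(0) mu2(1) sd1(2.08) sd2(2.08) m(4) rho(0.09) beta(0.9"). Per arm without clustering: 2 × [2.08 × (1.960 + 1.282)]² = 90.9. Design effect: 1 + 3 × 0.09 = 1.27. Settings per arm: 90.9 × 1.27 / 4 = 28.9, so 29. Allowing for 10% setting dropout: 29 / 0.9 = 32.2, so 33 per arm, which is 66 settings and 66 × 5 = 330 children. The stated size reproduces.

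**Inputs for the check.** After dropout there are 33 × 0.9 = 29.7 settings per arm with 4 children each, SD 2.08 and ICC 0.09, all from that section. The correlations of baseline with week 32, baseline with week 52, and week 32 with week 52 are assumptions, because the article gives none. Visit SDs are taken as equal and data as complete.

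**Formulas.** With all SDs scaled to 1, the true slopes are b32 = r(0,32) and b52 = r(0,52). Residual variances are v = 1 − r², and the residual covariance is c = r(32,52) − r(0,32) × r(0,52). Under an unstructured covariance, the shared slope b weights b32 and b52 in proportion to (v52 − c) and (v32 − c). Variance inflation at a visit is (visit slope − b)² / v. The imbalance left at 32 weeks is (b32 − b) × the baseline difference.

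**Size of a one-SE baseline difference.** 2.08 × √(2 × 1.27 / (29.7 × 4)) = 0.30 points.

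**Worked case (0.7, 0.5, 0.6).** v32 = 0.51, v52 = 0.75, c = 0.60 − 0.35 = 0.25. The weights are 0.50 and 0.26, so b = (0.50 × 0.7 + 0.26 × 0.5) / 0.76 = 0.632. Inflation is 0.068² / 0.51 = 0.9% at week 32 and 0.132² / 0.75 = 2.3% at week 52.

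| Assumed correlations (0–32, 0–52, 32–52) | Shared slope | Variance, wk 32 | Variance, wk 52 | Left at wk 32 per 1 SE of imbalance |
|---|---|---|---|---|
| 0.7, 0.7, 0.75 | 0.700 | 0.0% | 0.0% | 0.00 |
| 0.5, 0.4, 0.6 | 0.456 | +0.3% | +0.4% | 0.01 |
| 0.7, 0.6, 0.7 | 0.661 | +0.3% | +0.6% | 0.01 |
| 0.7, 0.5, 0.7 | 0.643 | +0.6% | +2.7% | 0.02 |
| 0.6, 0.4, 0.6 | 0.526 | +0.9% | +1.9% | 0.02 |
| 0.8, 0.5, 0.7 | 0.765 | +0.4% | +9.3% | 0.01 |
| 0.7, 0.3, 0.5 | 0.595 | +2.2% | +9.6% | 0.03 |
| 0.8, 0.4, 0.5 | 0.714 | +2.0% | +11.8% | 0.03 |
| 0.5, 0.7, 0.7 (order reversed) | 0.643 | +2.7% | +0.6% | −0.04 |

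When correlation decays, the loss is larger at week 52 because the likelihood pulls the shared slope towards the visit with less residual variance.

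**Power.** Take a trial with exactly 90% power at 32 weeks under separate slopes. With the shared slope, power is 89.8–89.9% for slope gaps of 0.1–0.3, 89.4% for (0.7, 0.3, 0.5) and 89.2% in the reversed case.

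**Comparison of the visits.** A one-SE imbalance contributes (b32 − b52) × 0.30 to the difference between the two visit effects: 0.06 points for a gap of 0.2 and 0.12 for a gap of 0.4.

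**Simulation.** Five scenarios were run with 58 settings of 4 children and 1,500 runs each. The mean 32-week estimate was within 0.004 of the true value of zero under either model. The ratio of empirical SDs (shared to separate) was 0.999–1.009. Type I error was 5.2–5.7% with either model.

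**The case against.** The strongest reply is that the premise is not in the article. A shared slope costs nothing if the slopes are equal, and the calendar cuts both ways: week 52 falls at the same time of year as baseline, and degenerative conditions are excluded, which favours stability. Slopes can also agree when correlations do not. With the week-52 SD 1.2 times larger, correlations of 0.7 and 0.6 give slopes of 0.70 and 0.72, and the loss vanishes. All of this stands, so the point can only be conditional.

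It can also be said that crossing a covariate with time is ordinary SAP detail, and that the SAP is not shown. That has force, and the SAP may already include the term. But the article commits to an explicit list that names one time interaction and omits its natural partner. Its provision for checking assumptions leads to transforming the data, not to adding a term.

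A reader might infer a larger loss at 32 weeks. If an equal-variance covariance were fitted, the two slopes would be weighted equally, giving 0.1² / 0.51 = 2% for baseline correlations of 0.7 and 0.5, and 0.2² / 0.36 = 11% for 0.8 and 0.4. The plan does not support this. Those same correlations imply residual variances of 0.51 against 0.75, and 0.36 against 0.84, and the AIC rule would see the gap. In a simulation with 238 children and no setting effect, AIC preferred unequal variances in 97.5% and 100% of 2,000 runs, provided such structures are among the candidates.

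Finally, the contrast between visits is not among the effects that the plan says it will extract. The carry-over into it matters only if someone reads the two visit effects against each other.

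**Conclusion.** The point holds as a minor, conditional one. The listed model does impose one baseline slope on both visits. If the true slopes differ, the loss under an unstructured covariance is about 0.3–2% of variance at 32 weeks (up to about 3% if the order is reversed) and about 0.4–12% at 52 weeks. The unadjusted remainder at 32 weeks, 0.01–0.04 points per SE of imbalance, compares with a 32-week SE of roughly 0.18–0.28 points and a target of 1 point.

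Two stronger inferences are not supported. The model does not automatically waste precision at both visits: the loss needs unequal slopes, which the article does not show. Nor does chance imbalance bias the primary result: most of it is still adjusted away, and over repeated randomisations there is neither bias nor inflated type I error.

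The figures rest on assumed correlations, equal visit SDs, complete data and the planning values for SD, ICC and dropout. Missing visits were not modelled.

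**What to change.** In the Primary analysis section, or in the SAP before outcomes are analysed, add a baseline-by-time interaction, so that the fixed effects contain baseline CCS, time, baseline-by-time, treatment arm and treatment-by-time. Use the same form for each continuous secondary outcome with a baseline score.

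The cost is one extra parameter per outcome and one line of text, with no new data. If the slopes turn out equal, almost nothing is lost: in the equal-slope simulation the two models had the same precision to within 0.1%.

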#### Primary outcome

The primary outcome is the Communication Complexity Scale (CCS) [11–13] completed at 32 weeks post-randomisation. The CCS was developed to describe and measure the development of pre-intentional and intentional communication in individuals with developmental disabilities and minimal verbal skills. It has demonstrated good reliability and validity in children with intellectual and developmental disabilities [12]. The CCS consists of a 12-point scale and covers three levels of early communication (pre-intentional, intentional non-symbolic and intentional symbolic), with higher scores reflecting more complex communication. Lower scores describe no response (0), alerting (1) or pre-intentional communication acts (2–5), scores of 6–10 are for intentional non-symbolic communication acts and scores of 11–12 are for intentional symbolic communication acts (e.g. using speech, signs or symbols; 11).

In the trial, the CCS will be used to score naturalistic sessions [14]. At each time point, the associated teacher will be asked to video themselves and the participating child or young person interacting for approximately 10 min following guidance provided by the trial team. Video recordings will be scored using the CCS by members of the research team who are blind to allocation. In line with training and guidance from the CCS developers, each video will be split into 30-s intervals, and each interval will be allocated a score of 0–12, i.e. the score for the highest scoring communication act within that interval. For scores of 6–12 (i.e. intentional communication), a function score will be allocated according to whether the function of the communication act was for ‘behaviour regulation’ (i.e. to bring about a specific result by requesting or protesting) or ‘joint attention’ (i.e. to direct a communication partner’s attention for social commenting; 11). An ‘optimal score’ will be calculated at each time point by averaging the three highest CCS scores [11]. The optimal score at 32 weeks post-randomisation will be the primary outcome and the optimal score at 52 weeks post-randomisation will be a secondary outcome.

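### If its model-checking rule is triggered, the primary CCS effect moves to a transformed scale that cannot be compared directly with the 1-point MCID behind the sample size

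*Protocol article*

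**What the plan says.** The Primary outcome section builds the endpoint from 30-second video intervals: "each interval will be allocated a score of 0–12". It then defines the endpoint itself: "An ‘optimal score’ will be calculated at each time point by averaging the three highest CCS scores". The score at 32 weeks is primary.

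The Primary analysis section fits a mixed linear model to this score at 32 and 52 weeks and then states: "Model assumptions will be checked, and if they are in doubt, the data will be transformed prior to analysis". The effect, overall and at each time point, "will be extracted in the form of an adjusted mean difference, 95% confidence interval and" *p* value. The section names no transformation, no criterion for doubt and no back-transformation. It does not keep a model estimate on the untransformed score.

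The Sample size {19} section works on the raw score: "Assuming a MCID of one point on the CCS [13], a standard deviation of 2.08 [12], 90% power, 5% alpha". The Stata command printed there uses a difference of 1 and an SD of 2.08.

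The opening of Statistical methods {27a} adds that every outcome will be described at each follow-up, with continuous data given as mean and SD.

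**The concern.** The score is bounded at 0 and 12. As an average of three whole numbers, it moves in steps of one third. Residuals from a linear model of such a score may not look normal, so a rule that responds to doubtful assumptions matters.

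The protocol's response is to change the scale of the primary endpoint before the primary estimate is made. Whether assumptions are in doubt can be judged only from outcome data, and the protocol gives no criterion. The trial was sized to detect one CCS point. After a non-linear transformation, the estimate and its confidence interval would be in other units, with no stated way of reading them against that point.

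**Working it through.** **1. The plan's own figure, to confirm its scale.** Inputs from Sample size {19}: difference 1, SD 2.08, power 90%, alpha 5% (sidedness not stated; two-sided assumed), 4 children analysed per setting, ICC 0.09.

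- Children per arm before clustering: 2 × [2.08 × (1.960 + 1.282) / 1]² = 90.9.
- Design effect: 1 + (4 − 1) × 0.09 = 1.27.
- Settings per arm: 90.9 × 1.27 / 4 = 28.9, so 29. With a t distribution (58 df), 30 per arm gives 90.1% power.
- Allowing for setting attrition: 60 × 1.1 = 66, the stated number. (60 / 0.9 = 66.7 would give 67; the difference is immaterial here.)

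The sample size is reproduced, and it is a raw-score calculation throughout.

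**2. What one CCS point becomes after transformation.** For a function f, the value is f(y + 1) − f(y). The protocol names no transformation, so two common ones are shown as examples.

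| Starting score y | log(1 + y) | square root |
|---|---|---|
| 2 | ln(4/3) = 0.288 | √3 − √2 = 0.318 |
| 5 | ln(7/6) = 0.154 | √6 − √5 = 0.213 |
| 9 | ln(11/10) = 0.095 | √10 − √9 = 0.162 |

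Between scores of 2 and 9 the value of one point differs by a factor of 0.288 / 0.095 = 3.0 on the log and 0.318 / 0.162 = 2.0 on the square root.

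**3. The reverse direction.** Suppose the log(1 + y) model gives a ratio of 7/6 = 1.167, which is one point at a score of 5. The implied gain at score y is (y + 1) × (1/6): 0.5 points at 2, 1.5 at 8 and 1.83 at 10. One transformed result therefore sits below, at or above the MCID depending on the reference score.

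**4. Is transformation needed for a valid test?** The expected analysed sample is 330 × 0.9 × 0.8 = 237.6, about 238 children. A simulation used 30 settings per arm, 4 children each, ICC 0.09, SD 2.08, scores rounded to thirds and clipped to 0–12, with a t-test on setting means (4,000 replicates per case). For assumed means of 1.5, 3, 7 and 10.5, type I error on the raw score was 4.7%, 4.4%, 5.1% and 4.8%. The means and the clipped-normal shape are assumptions, because the protocol gives no expected CCS mean or distribution. The test was also simpler than the planned mixed model. Within those limits, floor and ceiling effects did not invalidate the raw-score comparison.

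**The case against.** The strongest reply is that the statistical analysis plan will settle this. The protocol article says such a plan will be developed ahead of analysis, reviewed by the oversight committees and submitted as a protocol update. The trigger, the transformation and the back-transformation are details usually placed there. That is fair for those details. It does not dispose of the point, because the protocol has already fixed transformation as the remedy and placed it before the primary estimate. An analysis plan that follows the sentence inherits the problem.

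Other parts of the reply stand and limit the claim:

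- A reader might infer that a transformed result could not be read against the MCID at all. That goes too far. Raw means by arm will be reported, though unadjusted. A points value could also be recovered at a reference score, or by averaging model predictions over the sample. The protocol simply provides for neither of the last two.
- A reader might infer that the Primary analysis section breaks a promise of an effect in CCS points. It gives no unit. The point scale comes from the outcome definition and the sample size, so this is a tension between sections.
- A reader might extend the problem to the cost-effectiveness results that use the CCS. Nothing says that a transformed score would enter that analysis, which has its own methods and its own plan.
- The three-fold factor and the need for an offset at a score of 0 belong to logarithms. The square root gives about two-fold and needs no offset.
- The rule may never be triggered.

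**Conclusion.** The concern holds in conditional form. If assumptions are judged doubtful and a non-linear transformation is used, the primary adjusted mean difference is on a scale adopted after outcome data were seen. It then cannot be compared directly with the 1-point MCID and the SD of 2.08. The size depends on the transformation: across scores 2 to 9, the value of one point varies about three-fold on log(1 + CCS) and about two-fold on the square root.

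The stated sample size is unaffected. The check does not show that the rule raises the type I error; it shows only that the untransformed comparison kept it close to 5% under the assumed distributions. The conclusion rests on the sentence being applied as written.

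**What to change.** Replace the sentence on transformation with:

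> The primary estimate is the adjusted mean difference in optimal CCS points at 32 weeks, whatever the residual diagnostics show. If assumptions are in doubt, the same model is also reported with standard errors robust to clustering by educational setting, and any analysis of a transformed score is a sensitivity analysis only.

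This names one method for the doubtful case, so no further choice is left until after the data are seen. The statistical analysis plan should carry the same wording.

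The cost is one sentence and one extra sensitivity table. Robust standard errors do not repair a misspecified mean model on a bounded scale, nor a wrong missing-data model, which matters with 20% loss expected among children. Those issues need their own sensitivity analyses.
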